## Abstract

**Background:**

The number of colorectal cancer patients increases with age. The decision to go through major surgery can be challenging for the aged patient and the surgeon because of the heterogeneity within the older population. Differences in preoperative physical and cognitive status can affect postoperative outcomes and functional recovery, and impact on patients’ quality of life.

**Methods / design:**

A prospective, observational, multicentre study including nine hospitals to analyse the impact of colon cancer surgery on functional ability, short-term outcomes (complications and mortality), and their predictors in patients aged ≥80 years. The catchment area of the study hospitals is 3.88 million people, representing 70% of the population of Finland. The data will be gathered from patient baseline characteristics, surgical interventional data, and pre- and postoperative patient-questionnaires, to an electronic database (REDCap) especially dedicated to the study.

**Discussion:**

This multicentre study provides information about colon cancer surgery’s operative and functional outcomes on older patients. A further aim is to find prognostic factors which could help to predict adverse outcomes of surgery.

**Trial registration:**

ClinicalTrials.gov (NCT03904121). Registered on 1 April 2019.

**Supplementary Information:**

The online version contains supplementary material available at 10.1186/s12885-021-08454-8.

## Introduction

### Background and rationale

The proportion of older people is increasing rapidly in western countries. In Finland, the estimated portion of the population aged over 70 will increase from the current 15.8 to 20% in 2030 and 25% in 2070 [1]. As the incidence of colon cancer increases with age [1, 2], the number of colon cancer patients can also be expected to increase, although the incidence has not dramatically changed over the decades [2].

The primary recommended treatment for colon cancer is surgery [3], but the decision to go through a major operation can be challenging for both the aged patient and the surgeon. Therefore, age-related concerns may lead to undertreatment of older patients, who compose a heterogeneous group with vastly different physiological and cognitive performance status [4]. Many older patients may have significant comorbidities, poor nutritional, and functional status [5, 6], which have been associated with severe postoperative complications associated with reduced 30-day and 1-year survival after colon cancer surgery [7]. Careful assessment is therefore required to make individual treatment decisions [8].

Modern medical and operative developments, including perioperative anaesthesia care, surgical performance (laparoscopy, technical standardisation), enhanced recovery program (ERAS) and oncological treatments, have improved outcomes for aged colorectal cancer patients [9, 10]. The difference in short-term postoperative mortality between older and younger colorectal patients has reduced during the last decade [11]. Conversely, frailty, a state of diminished physiological reserve capacity [12], has been identified as a significant predictor of postoperative complications leading to a prolonged hospital stay, discharge to nursing homes or long-term care facilities, and higher mortality rates than for fit patients [13, 14]. Preoperative screening tests for evaluating malnutrition, functional performance status, anaesthesiologist risks, and the cumulative burden of comorbidities can help identify factors that increase the risks of postoperative adverse events. However, comprehensive geriatric evaluations are often time-consuming and demand resources, highlighting the need for easily implemented screening tools, which produce crucial and objective results [15].

Older patients commonly prioritise functional outcomes before survival after cancer surgery [16]. Recent studies from the Netherlands and Norway reported positive impacts on quality of life after surgery for aged patients with colorectal cancer [17, 18]. There is growing evidence that physical and mental prehabilitation strategies, together with innovative surgical and postoperative treatments, can enhance long-term outcomes, functional recovery, and quality of life after surgery [19, 20]. A recently published international multicentre prospective study, Geriatric Oncology Surgical Assessment and Functional rEcovery after Surgery (GOSAFE), showed that 68.4% of patients over 70 years experiencing cancer surgery are frail. Thus, frailty evaluation has an essential role in predicting postoperative morbidity and mortality correlating with quality of life and physical and cognitive functional recovery [21].

There is little prospectively collected published data about the influence of colorectal surgery on postoperative outcomes and functional recovery for very old patients. The consensus recommendations and studies are mainly made for patients over 70 years [4, 8, 21]. Patients over 80 years are seldom included in prospective clinical trials, so the optimal treatment of these patients remains unclear [22]. In Finland, the incidence of colon cancer patients over 80 years has increased from 183 to 216 per 100,000 in the past 20 years, and 28% of patients were aged 80 years or more in 2018 [23]. Thus, it is significant to have adequate and trustworthy information about colon cancer surgery and its effect on postoperative morbidity, functional recovery, and survival. Recognition of frailty is essential to reduce adverse outcomes. Preoperative real-life clinical data can provide objective and helpful measures to the surgeons planning interventions for aged patients [24]. These instruments should accurately predict surgery’s adverse outcomes and be easy to implement, and thus able to guide comprehensive decision-making [25].

### Objectives

This multicentre study aims to analyse the impact of colon cancer surgery on patients over 80 years, their functional ability, the occurrence of complications, and mortality during the first postoperative year and highlight predictors of these adverse outcomes. We also aim to investigate non-operatively treated patients’ progress and subsequent functional ability and survival [26].

## Methods

### Study design and setting

The study is an observational, prospective, cohort, multicentre study of patients aged 80 years or older diagnosed with stage I-III colon cancer. The patients are treated either non-operatively or with curative resection or a palliative procedure. The participating hospitals are Helsinki University Hospital, Tampere University Hospital, Turku University Hospital, Central Finland Central Hospital, North Karelia Central Hospital, Päijät-Häme Central Hospital, Satakunta Central Hospital, South Ostrobothnia Central Hospital and Vaasa Central Hospital. The catchment area of the study hospitals is 3.88 million people (of whom 219,900 are aged 80 years or over), representing 70.4% of Finland’s population [1].

The public health care system almost exclusively performs the treatment of malignant diseases in Finland. All citizens have equal access to health care independent of social or insurance status. These study hospitals represent majority of Finnish hospitals operating colon cancer patients. Hence, the study provides a nationwide spectrum of operative management of colon cancer on the aged population. The study is independent of any industrial sponsorships.

### Participants

Patients aged 80 years or over with recently diagnosed stage I-III colon cancer will be assessed for suitability for inclusion. General practitioners or endoscopic units make most consultations of colon cancer patients, so the data includes only the patients referred to surgical units for operative treatment.

### Eligibility criteria (Fig. 1)

#### Inclusion criteria

Stage I-III colon cancerAge 80 years or older at the time of recruitmentThe study’s information is approved and signed by the patient, or a legally authorised representative or family member if the patient’s cognitive status has declined.

**Fig. 1 Fig1:**
[figure not shown]
Eligibility criteria

#### Exclusion criteria

Metastatic cancer of any type at the time of diagnosis with no possibility of curative surgeryPatient undergoing emergency operation for colon cancerThe patient has an expected life expectancy of less than 6 months due to colon cancer or other reasons.

### Primary intervention

All the patients have a preoperative colonoscopy, computed tomography, and presentation at a multidisciplinary team (MDT) meeting. They will undergo either radical surgery or a palliative procedure for the primary tumour, or nonoperative treatment according to hospital-standardised protocols for treatment and follow-up based on national EBM guidelines [27, 28]. The decision for definitive treatment choice is made collectively with the patient or, when needed, with a family member or legally authorised representative.

### Tools for preoperative risk assessment

G-8: Onco-geriatric screening tool includes eight items modified from MNA-SF, age, number of medications and self-rated health status [31]. The G-8 score ranges from 0 to 17. Geriatric evaluation is recommended for patients whose score is ≤14 [32].

MNA-SF: Mini Nutritional Assessment-Short Form describes nutritional status as the normal, risk of malnutrition or malnourished. The score ranges from 0 to 14 and with cancer patients from 0 to 12. The risk of malnutrition is scored between 8 and 11 and malnourished patients between 0 and 7 [33].

CFS: Canadian Study on Health and Aging Clinical Frailty Scale, as assessed by the surgeon. The scale ranges from 1 to 9. Patients are described as frail with score ≥ 4 [34].

ASA: American Society of Anaesthesiologists physical status classification, which evaluates preoperative anaesthesiologist risk. The score ranges from 1 to 5. Categories are divided as 1 (a normal healthy patient), 2 (a patient with mild systemic disease, age > 65 years), 3 (a patient with severe systemic disease that is not incapacitating), 4 (a patient with an incapacitating systemic disease that is a constant threat to life), 5 (a dying patient who is not expected to survive for 24 h with or without operation) [35].

AA-CCI: Age-adjusted Charlson comorbidity index, which identifies cancer patients with increased risk of perioperative mortality. The scale ranges from 4 to 15; solid tumour excluded with two points, all patients 80 years or older contribute four points [36].

### Other information

Table 1 shows the information that is collected in addition to the risk assessment tools. The study surgeons record each patient’s baseline and data related to the surgery, perioperative hospitalisation, postoperative complications, and mortality. Patient-related questionnaires (Additional file 1) are collected before surgery, one, three, six and twelve months after surgery or the date non-operative treatment decision was made. The questionnaires will be collected either during the outpatient clinic visit, by telephone interview or by mail. All the information from the data mentioned above is recorded to the electronic database (REDCap) by the study surgeons. The dates and causes of death are obtained from the Death Certificate Register of Statistics Finland, which registers all deaths in Finland [37].

**Table 1 Tab1:** Collected information

	Preoperative	Surgery	Hospital stay	1 month	3 months	6 months	12 months
**PRE-AND POST-INTERVENTION DATA**							
Age	x						
Sex	x						
Height and weight, BMI	x						
Medication	x			x	x	x	x
ASA classification	x						
Clinical Frailty Scale-index (CFS)	x						
Comorbidities (include diseases subsumed in modifield Charlson Comorbidity Index)	x						
Haemoglobin, creatine, estimated GFR, albumin	x						
History of smoking and alcohol-consumption	x			x	x	x	x
Other reported cancers excluding colon cancer	x						
Diagnostic procedures (colonoscopy, CT scan)	x						
Onco-geriatric screening tool (G-8)	x			x	x	x	x
Mini Nutritional Assessment- Short Form (MNA-SF)	x			x	x	x	x
Status of living	x			x	x	x	x
Mobility	x			x	x	x	x
Neuropsychological status	x			x	x	x	x
Weight loss and food intake	x			x	x	x	x
Self-related health status	x			x	x	x	x
Patient information and approval	x						
**INTERVENTION DATA**							
Date of operation		x					
Used surgical technique (laparoscopy, open, conversion)		x					
Curative or palliative operation		x					
Demand for stoma		x					
Operative time and blood lose		x					
**POSTOPERATIVE DATA**							
Surgical complications (anastomotic leakage, bleeding, ileus, wound dehiscence or infection, other) Clavien-Dindo classification		x	x	x	x		
Non-surgical complications (cardiovascular, pulmonary, urinary, delirium, other) Clavien-Dindo classification		x	x	x	x		
Reoperations			x	x	x		
Length of stay			x	x			
Place of discharge			x	x			
Readmissions			x	x	x		
Pathological report (TNM-status)				x			
Postoperative adjuvant treatment				x	x	x	
Recurrences (local and distant)				x	x	x	x
Date of death							

### Recruitment

All patients aged 80 years or older who have been diagnosed with stage I-III colon carcinoma and are referred to participating hospitals to consider surgery are eligible for the study. Surgeons responsible for the treatment will inform the patients about the possible advantages and disadvantages of the intervention and the study protocol of patient-questionnaires during their visit to the outpatient clinic before the definitive treatment. The information and consent forms are specially designed for the study and include the surgeons responsible for recruitment at each study site. After properly informed consent is obtained, the patient is recruited to the study.

Non-operative treatment is chosen if the patient is deemed unfit to survive the operation due to anaesthesiologic, physiological or cognitive status. If necessary, an anaesthesiologist, cardiologist, the pulmonary or geriatric specialist is consulted in decision-making. Patients may also refuse surgery after receiving information about possible advantages and disadvantages of the procedure. The ultimate decision will be made collectively with the patient and, if possible, with relations.

Both non-operatively and operatively treated patients are included, and they are not randomised in any way.

### Allocation

The study is an observational, prospective study without randomisation. All patients who voluntarily sign the consent form are included in the study. According to standardised protocols for treatment and follow-up, they will be treated at the study hospitals based on national EBM guidelines [27, 28]. The excluded patients are not followed up.

### Questionnaires used in the study

The pre-and postoperative questionnaires are specially designed for the study and are all convergent. The questions survey living status, use of implements, outside personal aid, functional and cognitive ability, and nutrition utilising G-8, MNA-SF and CFS [31, 33, 34]. They are collected before surgery and one, three, six and twelve months after surgery. The use of large font size (Calibri 16) aims to help these older people to answer the questions. The questionnaires are writing in Finnish or Swedish thus patients can use their native language.

The questionnaires (Additional file 1) are composed of following questions:
status of living (home, nursing home, health centre wards)mobility (with or without implements, outside help)neuropsychological problemsnutrition (food intake, weight-loss)self-rated health status in comparison with other people of the same agenumber of medicationsnumber of hospital admissions 6 months before the index surgerysmoking habits and alcohol consumptionliving will (yes or no)

### Participant timeline

Recruitment started in April 2019 at Tampere University Hospital. The data collected from the participants and follow-up timeline is presented in Table 1. Short-term outcomes, including discharge history and complications, will be monitored at discharge, 1 and 3 months after primary operation by the surgeon responsible for recruitment.

### Sample size

The primary endpoints are the surgical and non-surgical postoperative complications and mortality. Previously published Finnish registry-based cohort studies on patients over 80 years with colorectal cancer reported complications rates 30–40% and severe complications 18–21%, respectively [7, 38]. In a large population-based cohort study with very old colorectal cancer patients, one-year mortality rates after surgery were 15–24% [39]. Frail patients had 2–3 times higher risk than non-frail patients of developing moderate to severe complications [14], leading to a disproportionately high risk of short-term mortality. A recently published study showed five times higher one-year mortality rate for patients with severe complications (8.6 vs 45%) [7].

Based on expected incidences of complications of 30% (fit patients) and 55% (frail patients), a sample size of 140 is needed to give 80% power to detect a significant difference between CFS 1–3 vs ≥ 4 groups, with two-sided type 1 error of 5%. Each group would comprise 70 patients. Additionally, with an estimated rate of one-year mortality of 10% (fit patients) and 25% (frail patients), we will need to study 113 frail subjects and 113 fit control subjects to be able to reject the null hypothesis that the failure rates for frail and fit subjects are equal with probability (power) 0.8. The type I error probability associated with this test of this null hypothesis is 0.05. We will use a continuity-corrected chi-squared statistic or Fisher’s exact test to evaluate this null hypothesis.

The first patient was included in the study 17th of April 2019 and operated on 29th April 2019. The preliminary estimate is that the final data will be collected by the end of April 2021.

### Data collection methods

#### Data management

An electronic database REDCap (https://www.project-redcap.org/) is used to gather the study data. REDCap is a secure web platform for building and managing online databases and surveys with online and offline data support. The main investigators have designed a dedicated version for this prospectively collected study data. All the surgeons responsible for the study at their hospital site receive a personal username and password for the electronic database to handle the data with confidentiality. Access to the whole database is limited to the main investigators in Tampere University Hospital and Tampere University.

All patients receive a study number, and the identification key is kept separately from the database on a username and password secured server at each study site. Data will be entered manually from paper case report forms (CRFs) into an electronic database (REDCap) protected by an automatic backup of server data and firewalls against external violation. All electronic case report forms (eCRFs) are handled with a particular study ID.

The occurrence of relevant protocol deviations such as metastatic disease, report of benign pathological tissue, or refusal to continue in the study will be determined and documented. Data verification and validation will be performed, and the results are analysed with code numbers not to identify the patient. When patient data and questionnaires have been coded, validated, and locked, a clean file will be declared.

#### Data collection

The principal investigator at each study site is responsible for the data collection and is reviewed by the main investigator. Each patient is asked to fill out patient-questionnaires at the time of inclusion, and at one, three, six and twelve months after surgery. If the patient cannot complete the questionnaire, a family member, legally authorised representative, or nurse in charge of the patient will complete the form. The principal investigators or research nurses of each study site are charged with ensuring that the patient questionnaires are completed.

Patients can resign from the study at any time during the study period, in this event data collected before resignation can be used in the analyses, following the last observation carried forward to practice.

#### Data monitoring

Instructions for data collection and storage have been provided to the surgeons responsible for recruitment at the study sites. The main investigator in Tampere University Hospital, who has full access to the full study register, will continuously monitor data. The other surgeons only have access to the patient register at their study site hospital. Technical and statistical monitoring, and advanced conduct with full access to the register, is given to the statistics expert from Tampere University.

#### Statistical methods

Percentages will be used to describe demographic data and the proportion of observed complications. The mean and standard deviation will be reported for age and the median and range for preoperative laboratory values and body mass index (BMI). Associations between the categorical variables are tested with the Chi-Square-test or the Fisher exact test, when appropriate. A uni- and multivariable analysis of the factors influencing morbidity and mortality will be carried out using binary logistic regression. All variables that were statistically significant in the univariate model are included in the multivariable model. Statistical analyses are performed using SPSS version 27.

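### Entering every univariably significant variable in the multivariable models makes the adjusted predictors unreliable, most of all for one-year mortality with about 40 expected deaths

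*Protocol article*

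**What the plan says.** Under Statistical methods, the protocol article states: "A uni- and multivariable analysis of the factors influencing morbidity and mortality will be carried out using binary logistic regression". The selection rule follows: "All variables that were statistically significant in the univariate model are included in the multivariable model". It covers both outcomes and makes no exception for CFS, the variable that defines the fit and frail groups in the Sample size section.

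Prediction is part of the study's purpose. The Objectives include the intention to "highlight predictors of these adverse outcomes", and the abstract's Discussion adds: "A further aim is to find prognostic factors which could help to predict adverse outcomes of surgery".

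For one-year mortality, the Sample size section assumes 10% in fit and 25% in frail patients and concludes that "we will need to study 113 frail subjects and 113 fit control subjects" for a test "with probability (power) 0.8". The same section names the test for that comparison: continuity-corrected chi-squared or Fisher's exact.

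The section on preoperative risk assessment tools describes G-8 this way: "Onco-geriatric screening tool includes eight items modified from MNA-SF, age, number of medications and self-rated health status". Table 1 also collects MNA-SF, age, medication, self-related health status, and weight loss and food intake as separate items.

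**The concern.** A univariable significance screen lets the same outcome data choose the model and then estimate it. Three things follow.

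- Variables with little or no true effect enter when chance favours them. Their estimates are then too large, because only large estimates pass, and the usual intervals ignore the selection.
- A variable that matters can be left out because it missed p<0.05 on its own. For mortality this includes CFS, for which the study was sized.
- If a composite score and its components are all candidates and all pass, they all enter one model, and their coefficients cannot be read separately.

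The fewer the events, the worse the first two become. The article's main Discussion says that the results could provide a basis for patient selection in later intervention studies, so unreliable predictors would be carried forward.

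**Working it through.** **1. The plan's own figure.** With 10% vs 25%, two-sided 5% and 80% power, the usual two-proportion formula gives 99.5 per group. The continuity correction n/4 × [1 + √(1 + 4/(n × 0.15))]² raises this to 112.5, so 113. The stated size is reproduced.

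**2. Expected events.**
- Deaths at the planning rates: 113 × 0.10 + 113 × 0.25 = 11.3 + 28.25 = 39.6.
- Deaths if the cited 15–24% applies to all 226: 33.9 to 54.2.
- Complications of any grade at 30% and 55%: 113 × 0.30 + 113 × 0.55 = 96.
- Severe complications at the cited 18–21%: 226 × 0.18 = 40.7 to 226 × 0.21 = 47.5. A model for severe complications would therefore be about as short of events as the mortality model.

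**3. Events per candidate.** The article gives no candidate list. Counting the preoperative items in Table 1 and the risk tools, without consent and diagnostic procedures, gives about 22. This is a reading, not a stated number.

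| Candidates | Deaths per candidate (39.6) | Complications per candidate (96) |
|---|---|---|
| 10 | 4.0 | 9.6 |
| 15 | 2.6 | 6.4 |
| 22 | 1.8 | 4.4 |

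**4. How many parameters the events support.**
- At the conventional 10 events per parameter: 39.6/10, about 4 for mortality; 96/10, about 9 for complications.
- A shrinkage target S = 0.9 at n = 226 gives p = n(S − 1)ln(1 − R²/S). For mortality the maximum R² is 0.604. An assumed Nagelkerke R² of 0.15, 0.20 or 0.30 then allows about 2, 3 or 5 parameters.

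**5. Can CFS be screened out?** Summing over all possible 2×2 tables with 113 per group and true rates of 10% and 25%, the univariable logistic Wald test reaches p<0.05 with probability 0.851. CFS, dichotomised as in the Sample size section, therefore fails the screen about 15% of the time. The continuity-corrected chi-squared test has power 0.810 in the same calculation, in line with the plan.

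**6. False selections.** With k independent candidates of no effect, the chance that at least one passes is 1 − 0.95^k: 40% for k = 10 and 64% for k = 20.

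**7. Simulated size of the effect.** All runs use 226 patients; candidates, correlations and effects are assumed.
- *15 candidates, mortality 17.5%:* five frailty scores correlated 0.4 or 0.6, and five modest true effects. The mean calibration slope in new data was about 0.66, and AUC was 0.73 apparent against 0.65–0.66 in new data. Coverage of 95% intervals, given selection, was 96–98% for the stronger predictors, 87–92% for weaker true ones and about 14–38% for unrelated null variables. A true log odds ratio of 0.2 was estimated on average at about 0.48.
- *18 candidates:* the slope was about 0.67 for mortality and 0.79 at the complication rate.
- *Stated rule against a fixed four-variable model containing the main predictor (18 candidates, mortality, two runs):* slope 0.67–0.68 against 0.78–0.81; new-data AUC 0.631–0.636 against 0.648–0.654.

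**The case against.** The strongest defence is that the study's sized comparison does not use this model. CFS 1–3 against ≥4 is compared by chi-squared or Fisher's exact test, and complication and mortality rates are reported whatever the regression does. That stands. A reader might infer that the rule undermines the fit-versus-frail result, but the Sample size section shows otherwise. What can be lost is the adjusted CFS estimate in the mortality model. Missing p<0.05 is indeed a limit of power, but a fixed model would still report that estimate with its interval.

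A reader might also infer that all confidence intervals from these models are invalid. The simulations do not support that: stronger predictors kept near-nominal coverage. Low coverage for null variables is close to automatic once one conditions on their having passed the screen.

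Nor does the article say that every item in Table 1, or every tool together with its components, will be a candidate. The overlap of G-8 with its components is conditional on all being tried and all passing. An article may leave the candidate list to a fuller document, so the missing list is not the fault. The stated selection rule is.

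Finally, about 40 deaths is an expectation at the planned size with an even split, which an observational cohort does not guarantee. More recruits, or deaths among non-operated patients, would raise it. The measured gain in new-data AUC from a fixed model is modest. These points limit the size of the problem but do not make the rule sound.

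**Conclusion.** The concern holds for the adjusted models. The article states a selection rule without exception for an analysis that serves a declared aim, and the rule is a poor one at the implied number of events. It is most damaging for one-year mortality, at 39.6 expected deaths (34 to 54 under the cited rates), and milder for complications of any grade, at about 96.

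Two results rest on the article's own figures: the event counts and, with CFS dichotomised, the roughly 15% chance that CFS drops out of the mortality model. The calibration slopes (about 0.67 for mortality, 0.79 for complications), AUC losses and coverage figures depend on assumed candidates and effects. They show direction and likely order of size only.

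The harm to intervals and odds ratios falls mainly on weak or null variables that pass the screen. A parameter limit derived from deaths should not be carried over to the model for complications of any grade.

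**What to change.** Replace the selection sentence under Statistical methods before the models are fitted, and record the change as an amendment:

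- For each outcome, pre-specify the covariates on clinical grounds, with CFS always included.
- Match the number of parameters to that outcome's events: about 4 for mortality and about 9 for complications of any grade at 10 events per parameter. Recalculate from the observed event totals, or if morbidity is modelled as severe complications. Alternatively, fix a larger list and use penalised estimation (ridge or Firth).
- Assess overlapping tools, such as G-8 and MNA-SF, in separate models, each added to the same base model.
- Keep the univariable results as description, not as a gate.
- If a model is presented as predictive, report bootstrap optimism-corrected discrimination and calibration.

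This needs no new data. It costs wording, a little more analysis and fewer variables in the headline model.
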